### Intervention

Ulcus Cruris Care is a multifaceted intervention aiming to implement a disease management concept for outpatient treatment of VLU patients in GP practices. The intervention comprises four major components shown in Table 3.

**Table 3 Tab3:** The intervention components in “Ulcus Cruris Care”

Components of the intervention “Ulcus Cruris Care”	
1	Online training and e-learning courses for GP practices
2	Standard operating procedures for VLU treatment
3	Software support for VLU disease management
4	E-learning courses and printable information for patient education

*VLU* venous leg ulcer

Participating GPs and medical assistants will receive joint online training via webinar according to a synchronous concept comprising 2 teaching units of 45 min each. In addition, asynchronous target-group-specific e-learning courses are provided via an online platform (https://welearn.academy). Online training and e-learning are mandatory to be completed before inclusion of the first patient and will be tracked via documentation and within the online platform. The didactic interventions are designed to support the implementation of a standardized disease management process for VLU patients in GP practices. Under GP supervision, medical assistants are intended to take a central role in wound treatment and patient monitoring and education. Central learning content comprises wound assessment, compression therapy, local wound therapy, and patient education. As a secondary learning objective, practical skills of correctly applying and assessing a compression bandage are to be conveyed. An online video demonstrating the application of compression bandages is integrated in the e-learning course, which is online available at any time. Online training and e-learning courses were designed and reviewed by physicians from the department for general practice and the department for dermatology at the University Hospital of Heidelberg.

To support standardized treatment, the practices are provided with standard operating procedures based on current guidelines for medical compression therapy, wound cleaning and local wound treatment for VLU.

A software support for wound documentation and patient monitoring was developed by the Department of General Practice and Health Services Research and is integrated into the case management software *care cockpit,* which has been developed for routine use in German GP practices [17]. Main function of the software module is a standardized monitoring of compression therapy, wound status, and patient education. Treatment success and wound healing can be checked via a progress overview. In addition, the creation and adaptation of a standardized treatment plan and scheduling of monitoring visits and recall is supported.

Patients are given access to a plain-language e-learning course and print-based information (asynchronous concept). The main content of the patient education comprises an introduction to VLU disease, compression therapy, local wound treatment, exercises, and general measures such as skin care and nutrition and are intended to support informed and active participation in the treatment process for patients and relatives. A video demonstrating application of compression bandages and step-by-step instructions for wound dressing changes and exercises are integrated in the e-learning course and are online available at any time. Patient education will be addressed in a standardized manner within monitoring visits in order to give regular opportunities to clarify open questions and promote active participation in the treatment process.

All intervention components are will be implemented on the practice level and are intended to support the treatment of patients with VLU in GP practices. Treatment and patient education fall under full responsibility of the treating physicians of the participating GP practices. Consequently, no unintended adverse effects are to be expected from the interventions.

### Control

No intervention will be performed in GP practices randomized to the control arm and included patients will receive usual care.

### Allocation concealment and blinding

Due to the character of the intervention, blinding of GP practices and patients is not feasible. Participating patients will not actively be informed about the allocation of their treating GP practice. However, it may be recognized if patients receive printable information material or access to patient e-learning as a part of the intervention. Investigators analyzing the primary outcome are blinded to group allocation.

#### Primary outcome

The primary outcome is the time from baseline to ulcer healing defined as complete re-epithelialization with no scab remaining. In case of multiple ulcers, all venous leg ulcers of both legs must meet the criteria of ulcer healing. Assessment of ulcer healing will be performed during regular visits in treating GP practices. If the criteria for ulcer healing are met according to judgment of treating physicians, pseudonymized photo documentation of the same day will be transferred to the study center. The photo documentation must comprise both legs in front and back view as well as close-ups of all leg ulcers. Two independent and blinded investigators who are qualified GPs will review the photo documentation to assess ulcer healing. In case of dissent, a third blinded investigator will be consulted for settlement. If ulcer healing is verified by two investigators, the date of the photo documentation will be recorded as the date of ulcer healing. If healing cannot be verified, treating physicians are informed and the verification process will be repeated weekly for 4 weeks. If the ulcer healing remains unaccomplished, initiation of the verification process will be repeated upon reassessment of the treating physician.

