### Study population and eligibility criteria

Approximately 800 regional GP practices collaborating with the study center will be approached by information letters. Interested GP practices will be screened for inclusion by investigators from the study center according to eligibility criteria for GP practices shown in Table 1.

**Table 1 Tab1:** Eligibility criteria for GP practices

Inclusion criteria	Exclusion criteria
• At least one medical assistant is routinely involved in chronic wound treatment and care	• No involvement of medical assistants in chronic wound treatment and care
• IT requirements for using the CareCockpit software met	• GP practices with more than 20 VLU patients per year
	• IT requirements for the use of the CareCockpit software not met
	• no declaration of consent given

*VLU* venous leg ulcer

Eligible physicians and medical assistants will be introduced to the trial via an information sheet and telephone contact for informed consent. Included GP practices are intended to recruit patients with at least one florid venous leg ulcer. Screening and review of patient eligibility will be performed by the responsible primary care physicians of included GP practices. Patient eligibility criteria are shown in Table 2.

**Table 2 Tab2:** Eligibility criteria for patients

Inclusion criteria	Exclusion criteria
• Patient with VLU or mixed ulcer of predominantly venous origin	• Florid leg ulceration of other origins
• Ulcer duration ≤ 6 months	• Ulcer duration > 6 months (182 days)
• Age ≥ 18 years	• Ankle Brachial Index of affected lower extremity < 0.5 or ankle artery pressure < 60 mmHg
	• Decompensated heart failure (≥NYHA III)
	• Immobility
	• Age < 18 years
	• No ability to give consent

*VLU* venous leg ulcer

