#### Secondary outcomes

Baseline parameters and the secondary outcomes are determined at baseline (T0), 3 (T1), and 12 months (T2) after patient inclusion (Table 4).

**Table 4 Tab4:** Secondary outcomes

***Outcome***	***Time of measurement***
Number of patients with complete ulcer healing	T1, T2
Number, size of ulcers [cm^2^]	T0, T1, T2
Ulcer recurrence	T1, T2
Pain according to visual analog scale	T0, T1, T2
Health-related quality of life, assessed using the validated questionnaire (EQ-5D-5L)	T0, T1, T2
Depressiveness according to the validated Patient Health Questionnaire (PHQ-9)	T0, T1, T2
Patient satisfaction and information, assessed using the “Patient Assessment of Chronic Illness Care” (PACIC-5A)	T0, T1, T2
Adherence to venous leg ulcer treatment	T1, T2

T0 = baseline, T1 =3 months after inclusion, T2 = 12 months after inclusion

The number of patients with complete ulcer healing will be assessed according to the criteria defined for the primary outcome. Furthermore, the number and sizes of VLU will be assessed. Wound size is determined by the perpendicular method measuring the greatest length and greatest width in cm in perpendicular axes at time points T0, T1, and T2. Ulcer recurrence is defined as the occurrence of any new venous leg ulcer during the observation time. Pain intensity will be measured using the visual analog scale. To assess health-related quality of life, the validated EQ-5D-5L questionnaire of EuroQol Group will be used. Depressiveness will be assessed using the validated Patient Health Questionnaire (PHQ-9) [18]. The Patient Assessment of Chronic Illness Care (PACIC-5A) is used to survey patient satisfaction and quality of patient education [19]. Adherence to VLU treatment elements is assessed by the patient and by caregivers using a Likert scale of 1–5 (non-adherent to adherent) for attendance of appointments and implementation of caregiver recommendations for local wound treatment, change of wound dressings, and general measures. In order to identify barriers to adherence, a free text field is provided to facilitate an indication of individual problems with therapy elements.

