#### Statistical analysis

The statistical analysis is carried out using a validated R environment with software version ≥ 4.0. The analysis of the quantitative data is performed according to scientific standards. The description of the baseline data will use appropriate descriptive measures such as mean, standard deviation, minimum, median, interquartile range and maximum for continuous parameters and scores, and using absolute and relative frequencies for categorical data. Homogeneity of the study arms will be evaluated by *t* test and chi-square test as appropriate.

The primary outcome “time to ulcer healing” is analyzed using a Cox proportional hazards regression model (shared frailty model) at a two-sided significance level of *α* = 5%. The variables “group,” “ulcer size,” “duration of VLU,” and “BMI” are included as fixed effects and the variable “practice” as a random effect. The use of this model generally increases the power compared to an ordinary log-rank test. Furthermore, the effect size is given by means of a point estimator (hazard ratio and rate difference at 12 weeks) with an associated 95% confidence interval. Further sensitivity analyses include the consideration of the cluster structure via averaging (per practice) and further regression models.

A non-inferiority analysis will be applied to the cost data, in order to determine whether the costs of care incurred in by the intervention group can be considered as high as or lower than the costs of care incurred in by the control group. The ICER will be calculated on the basis of the costs and effects of the intervention and control group as follows:
$$ \mathrm{ICER}=\frac{\varnothing \mathrm{costs}\ \mathrm{of}\ \mathrm{care}\ \mathrm{intervention}\ \mathrm{group}-\varnothing \mathrm{costs}\ \mathrm{of}\ \mathrm{care}\ \mathrm{control}\ \mathrm{group}}{\varnothing \mathrm{effects}\ \mathrm{intervention}\ \mathrm{group}-\varnothing \mathrm{effects}\ \mathrm{control}\ \mathrm{group}} $$

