## Trial status

The trial will be conducted according to the presented protocol (version 1 as of July 19, 2021). Recruitment of GP practices will begin in the 4th quarter of 2021 and is planned to be finished until the end of 2nd quarter of 2022. Patient recruitment is scheduled for the 12-month period of 2022. The results of the UCC trial are expected for the 1st quarter of 2024 and will be communicated via publications, the website of the trial (https://ulcuscruris.care), and the German clinical Trials Register.

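### Trained intervention practices may already be treating an ulcer before T0, so programme care can act before the healing clock starts, in one arm only

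*Protocol article*

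**What the plan says.** - **Clock.** Primary outcome: "The primary outcome is the time from baseline to ulcer healing defined as complete re-epithelialization with no scab remaining". Secondary outcomes: "Baseline parameters and the secondary outcomes are determined at baseline (T0), 3 (T1), and 12 months (T2) after patient inclusion".
- **Programme.** Intervention: "Online training and e-learning are mandatory to be completed before inclusion of the first patient". The components are to be "implemented on the practice level and are intended to support the treatment of patients with VLU in GP practices". Under Control, no intervention is performed in control practices.
- **Entry.** Table 2 admits "Ulcer duration ≤ 6 months" and does not require that the ulcer be new to the practice. On who enrols: "Screening and review of patient eligibility will be performed by the responsible primary care physicians of included GP practices". Trial status: "Patient recruitment is scheduled for the 12-month period of 2022". A practice may enrol up to 5 patients (Recruitment and trial timeline); about 3 are planned (Sample size).
- **Model.** Statistical analysis, on the primary Cox model: "The variables “group,” “ulcer size,” “duration of VLU,” and “BMI” are included as fixed effects". Practice enters as a random effect. Table 4 lists ulcer size at T0, so I read the size covariate as the T0 value.

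**The concern.** Randomisation is by practice, but time zero is set patient by patient, possibly months after the practice was trained. Suppose an intervention practice is trained in January and in August enrols a patient whose ulcer it has treated for 3 months. That ulcer may have had trained care for 3 months before its clock starts. A comparable control ulcer has had usual care only.

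Two things follow for such patients. Ulcers that close quickly under the programme are gone before they can be enrolled, so those that enter are a selected remainder. And the ulcer's size at T0 may already reflect allocation, so adjusting for it is no longer adjustment for a pre-randomisation variable. Both arise even if every eligible patient is enrolled consecutively, so this is separate from whom the physician chooses.

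The study hypothesis is that implementing the programme in practices leads to faster healing. Healing gained before T0 is outside the primary outcome, and outside the 12-month cost horizon, which also starts at T0.

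**Working it through.** **1. The plan's own figure.** From Sample size: 60% and 80% healed at 12 weeks, exponential curves, 20% drop-out, 80% power. From Statistical analysis: two-sided alpha 0.05.

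- HR = ln(0.2)/ln(0.4) = 1.756.
- Freedman events = (1.960 + 0.842)² × ((1 + 1.756)/(1 − 1.756))² = 104.2.
- With 52 weeks of follow-up (assumed from T2) and the 20% drop-out spread over them, the mean event probability is 0.950.
- 104.2/0.950/2 = 54.8, so 55 per arm. The stated 55 reproduces.

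**2. Pre-T0 exposure under the plan's exponential assumption.** The hazard does not depend on elapsed time, so 1 − S(g+12)/S(g) = 1 − S(12) for any lag g. The contrast from T0 stays 60% v 80%, HR 1.76. What differs is who is left to enrol: with g = 4 weeks, 1 − 0.4^(1/3) = 26% of control and 1 − 0.2^(1/3) = 42% of intervention ulcers have healed before T0.

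**3. With heterogeneous healing.** These inputs are my assumptions: gamma frailty between patients with variance v of 0.5 or 1; 60%/80% calibrated from the first wound visit; the same lag g for every patient in both arms.

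S(t) = (1 + v·L·t)^(−1/v), with L set so that S(12) is 0.4 (control) or 0.2 (intervention). Healed within 12 weeks of T0 = 1 − S(g+12)/S(g).

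Example, v = 1, g = 4: L is 1.5/12 = 0.125 (control) and 4/12 = 0.333 (intervention). Control: 1 − 1.5/3.0 = 50.0%. Intervention: 1 − 2.333/6.333 = 63.2%. If programme care began only at T0 after 4 weeks of usual care: 1 − 1.5/5.5 = 72.7%.

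| Lag (weeks) | v | Control | Programme care before T0 | Difference | Programme care from T0 only | Difference |
|---|---|---|---|---|---|---|
| 4 | 0.5 | 54.8% | 71.6% | 16.8 | 75.9% | 21.1 |
| 4 | 1 | 50.0% | 63.2% | 13.2 | 72.7% | 22.7 |
| 8 | 0.5 | 50.3% | 64.5% | 14.2 | 72.0% | 21.7 |
| 8 | 1 | 42.9% | 52.2% | 9.3 | 66.7% | 23.8 |

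The 12-week average HR, ln(1 − intervention)/ln(1 − control), at a 4-week lag is 1.59 (v = 0.5) or 1.44 (v = 1) with programme care before T0, against 1.79 or 1.87 if it starts at T0. The loss comes from the programme acting early in one arm, not from the lag itself.

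**4. With progressive closure.** A small simulation (5 runs of 800 patients per arm) used Weibull healing times with shape 1.5, a 12-week lag in all patients and a noisy measure of T0 size. Unadjusted HR: 1.74 with programme care before T0, 1.47 if it starts at T0. Adjusted for T0 size: 2.01 and 1.96. With no lag the two set-ups are identical, yet they printed 1.82 and 1.78 unadjusted, and 2.22 and 2.29 adjusted. The adjusted gap of 0.05 is therefore within simulation noise; the unadjusted gap of 0.27 is not. Here smaller T0 ulcers favour the intervention, and adjustment removes nearly all of that.

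**The case against.** - **Exposure is possible, not shown.** It concerns only ulcers that a trained practice was already treating before inclusion. Ulcers enrolled at first presentation, managed elsewhere or treated only before training are unaffected, and the article does not give the share. Practices are screening and are compensated for study visits, which argues for prompt enrolment. This stands. If half the patients had the 4-week lag and half had none, simple averaging gives (20 + 16.8)/2 = 18.4 points for v = 0.5.
- **Full programme care before T0 is not shown.** Only training is placed before the first inclusion. The software monitoring, treatment plan and patient material may start for a given patient only at inclusion. This stands too. What can precede T0 is trained care under the practice's procedures.
- **The bias has no fixed direction.** A reader might infer that the hazard ratio is necessarily pulled towards no effect, and that adjusting for T0 size takes away more. The article supports neither. The plan's exponential assumption gives no change, and in the progressive-closure scenario adjustment removes a distortion instead of adding one. Nor are all covariates already treated: duration is affected only through enrolment timing or selective healing, and BMI not plausibly.
- **Part of the information exists.** Training completion is tracked and ulcer duration is recorded, so a patient's exposure is bounded by the shorter of ulcer duration and time since training. That is only an upper bound. A 3-month-old ulcer in a practice trained 7 months ago could have had anything from none to 3 months of trained care, and control practices have no matching date.
- **The full protocol may define enrolment timing.** It may, and if so it answers part of this. The point rests on what the article fixes: the eligibility window, time zero, training before inclusion and the covariates.

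**Conclusion.** The pathway follows from the plan's stated rules. Trained care can act before time zero in the intervention arm only, early-healed ulcers then never enter, and T0 ulcer size can be a post-randomisation covariate. The comparison from T0 may therefore be distorted.

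Neither the exposed share nor the size or direction can be fixed from the article. The fall from 20 to about 17 or 13 points assumes gamma frailty and a 4-week lag in every patient; it is an illustration at full exposure, not an estimate for this trial. The contrast from T0 remains a valid description of healing after inclusion. What is at risk is the comparability of the arms at T0 and the part of the effect that precedes it. It should be addressed at the design stage, because an analysis plan finished before database closure cannot supply a date that was never collected.

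**What to change.** 1. In both arms, record in the eCRF the date on which the practice first treated the index ulcer, and hold a practice start date: training completion, or a matching date in control practices.
2. Complete T0 before the software module or patient material is used for that patient, and say so in the protocol.
3. Ask practices to enrol at the first eligible wound visit where feasible, without a hard exclusion. A strict time limit would cost patients in a trial that already expects recruitment bottlenecks.
4. Add two sensitivity analyses of the primary outcome: one limited to patients with little or no treatment between the practice start date and T0 (for example at most 14 days), counted as T0 minus the later of the start date and the first-treatment date; and one without T0 ulcer size. Treat both as supportive, because the restricted set is itself formed after randomisation.

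The cost is one extra eCRF date, some extra analysis and lower precision in the restricted analysis. The sample size and the primary model can stay as they are.

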#### Secondary outcomes

Baseline parameters and the secondary outcomes are determined at baseline (T0), 3 (T1), and 12 months (T2) after patient inclusion (Table 4).

**Table 4 Tab4:** Secondary outcomes

***Outcome***	***Time of measurement***
Number of patients with complete ulcer healing	T1, T2
Number, size of ulcers [cm^2^]	T0, T1, T2
Ulcer recurrence	T1, T2
Pain according to visual analog scale	T0, T1, T2
Health-related quality of life, assessed using the validated questionnaire (EQ-5D-5L)	T0, T1, T2
Depressiveness according to the validated Patient Health Questionnaire (PHQ-9)	T0, T1, T2
Patient satisfaction and information, assessed using the “Patient Assessment of Chronic Illness Care” (PACIC-5A)	T0, T1, T2
Adherence to venous leg ulcer treatment	T1, T2

T0 = baseline, T1 =3 months after inclusion, T2 = 12 months after inclusion

The number of patients with complete ulcer healing will be assessed according to the criteria defined for the primary outcome. Furthermore, the number and sizes of VLU will be assessed. Wound size is determined by the perpendicular method measuring the greatest length and greatest width in cm in perpendicular axes at time points T0, T1, and T2. Ulcer recurrence is defined as the occurrence of any new venous leg ulcer during the observation time. Pain intensity will be measured using the visual analog scale. To assess health-related quality of life, the validated EQ-5D-5L questionnaire of EuroQol Group will be used. Depressiveness will be assessed using the validated Patient Health Questionnaire (PHQ-9) [18]. The Patient Assessment of Chronic Illness Care (PACIC-5A) is used to survey patient satisfaction and quality of patient education [19]. Adherence to VLU treatment elements is assessed by the patient and by caregivers using a Likert scale of 1–5 (non-adherent to adherent) for attendance of appointments and implementation of caregiver recommendations for local wound treatment, change of wound dressings, and general measures. In order to identify barriers to adherence, a free text field is provided to facilitate an indication of individual problems with therapy elements.

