### Statistical methods

#### Sample size

The sample size calculation is based on the primary outcome “time to complete wound healing (“time-to-heal”)”. Assumptions are based on the literature: a healing rate after 12 weeks of 60% is assumed in the standard care (control group) [23] and, based on clinical studies on patient-centered interventions, of 80% [24] in the intervention group. With a significance level of *α* = 0.05, an assumed drop-out rate of 20%, and the assumption of exponentially distributed healing curves, a sample size of *n* = 55 patients per study arm is needed to achieve a power of 80% when applying a log-rank test in the classic two-group comparison. In order to take the cluster structure of the data into account (patients in doctors’ practices), the sample size is further adjusted by a design effect of 1.1, which is calculated from a cluster size of *n* = 3 patients per practice and a conservative intra-cluster correlation coefficient (ICC) of 0.05. This results in a total sample size to be recruited for the study of *n* = 126 patients (*n* = 63 per group) in *n* = 42 practices (*n* = 21 per group). In addition, in order to prevent possible drop-outs or recruitment bottlenecks among the GP practices, the target number of practices to be recruited is increased to *n* = 50 (*n* = 25 per group). This will increase the power in the study, as a larger number of clusters has a positive effect on the design effect. The sample size planning was carried out using PASS software.

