A formula based on the Fieller’s theorem will be used to determine the 95% confidence interval (CI) of the ICER. Using the 95% CI, the cost-effectiveness of the intervention will be interpreted in light of several realistic cost-effectiveness thresholds. Costs and effects are discounted at a rate of 3% p.a. Moreover, discounting rates of 0% and 5% are applied in a sensitivity analysis. The cost-effectiveness may differ for various subgroups and variables unaffected by the intervention. These should be compared or controlled for statistically. To account for uncertainty in the measured parameters, both deterministic and probabilistic sensitivity analyses will be performed, where variables affecting the cost-effectiveness are randomly drawn from a distribution informed by observed data and academic literature.

The evaluation of further secondary outcomes will be carried out with appropriate descriptive measures and comparisons of the study groups using t-tests for continuous variables and chi-square tests for categorical variables. The corresponding effects are described using point estimators with associated 95% confidence intervals. The relationship between variables is checked using the Spearman correlation coefficient. Wherever appropriate, statistical graphs will be provided to visualize the results. Details of the statistical analysis will be further specified in a statistical analysis plan, which will be completed before database closure.

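### The count of patients healed at T1 and T2 can mean healed by the visit or ulcer-free at the visit, and the planned chi-square test ignores practice and cannot score unhealed drop-outs

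*Protocol article*

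**What the plan says.** Under Secondary outcomes, the protocol article introduces the outcomes as determined at T0, T1 and T2. Table 4 lists the number of patients with complete healing at T1 and T2. The only definition is one sentence: "The number of patients with complete ulcer healing will be assessed according to the criteria defined for the primary outcome".

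The Primary outcome section contains two different things. One is a state: re-epithelialization is complete without scab, and with several ulcers "all venous leg ulcers of both legs must meet the criteria of ulcer healing". The other is a dated event: when the treating physician judges that healing has occurred, photographs go to blinded reviewers, and once healing is verified "the date of the photo documentation will be recorded as the date of ulcer healing".

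Table 4 also lists the number and size of ulcers (T0, T1, T2) and, as a separate outcome, recurrence (T1, T2), meaning any new venous leg ulcer while the patient is observed.

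Under Statistical analysis, further secondary outcomes are compared using "t-tests for continuous variables and chi-square tests for categorical variables", with point estimates and 95% confidence intervals. The primary outcome, by contrast, has a shared frailty Cox model with practice as a random effect, and a rate difference at 12 weeks.

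**The concern.** A patient verified as healed in week 6 who has an open ulcer at month 12 is a success if the count is cumulative and a failure if it is current status. The plan expects such patients, because recurrence is an outcome of its own. Nothing says how to count them.

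The stated test adds two problems under either reading. It treats patients of one practice as independent, although the sample size allows for clustering. It also needs a yes or no for everyone: a patient lost unhealed in week 5 has an unknown status at T2, and the test can only exclude that patient or impute an answer. A time-to-event method uses the five weeks observed and then censors.

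At stake is the 12-month healing result. Readers will take it at face value, yet it could be cumulative or current, and if cumulative it may lie so near 100% in both arms that it says little.

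**Working it through.** **Inputs (Sample size section).** "a healing rate after 12 weeks of 60% is assumed in the standard care (control group"); "of 80% [24] in the intervention group"; "an assumed drop-out rate of 20%, and the assumption of exponentially distributed healing curves"; "With a significance level of *α* = 0.05", which the Statistical analysis section calls two-sided for the primary outcome. The section states 80% power with a log-rank test, 55 per arm before clustering, a design effect of 1.1 (3 patients per practice, ICC 0.05), and 63 per arm finally.

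**1. Reproduce the plan's figure.**
- Weekly healing hazards: −ln(0.4)/12 = 0.0764 (control) and −ln(0.2)/12 = 0.1341 (intervention). Hazard ratio 0.1341/0.0764 = 1.756.
- Freedman events: [(1.960 + 0.842) × (1.756 + 1)/(1.756 − 1)]² = 104.2, so 105.
- The article does not say how drop-out enters. Assume it is exponential, 20% over 52 weeks: hazard −ln(0.8)/52 = 0.0043 per week.
- Probability of observed healing in 52 weeks, λ/(λ+γ) × (1 − e^(−52(λ+γ))): 0.9325 and 0.9683.
- Patients per arm: 105/(0.9325 + 0.9683) = 55.2, against the stated 55. Cutting follow-up at 12 weeks gives 76.5.
- Clusters: 55 × 1.1 = 60.5, rounded up to 21 practices × 3 = 63.

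The stated 55 is therefore consistent with exponential curves run to 12 months, and not with curves cut at 12 weeks.

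**2. Healed-by reading on these curves.** Proportion healed by week w: 1 − 0.4^(w/12) and 1 − 0.2^(w/12).

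| Visit | Control | Intervention | Expected unhealed of 63 | Exact chi-square power, 63 per arm |
|---|---|---|---|---|
| T1 (13 weeks) | 62.9% | 82.5% | 23.3 and 11.0 | 71% |
| T2 (52 weeks) | 98.1% | 99.9% | 1.2 and 0.06 | 3% |

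Power is by binomial enumeration of the uncorrected test, without clustering. With no unhealed intervention patient, 3 unhealed controls give z = 1.75 and 4 give z = 2.03, so at least 4 are needed where 1.2 are expected.

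**3. Dependence on the constant hazard.** Assume the hazard after week 12 falls to a fraction f of its early value in both arms. Healed by week 52 is then 1 − 0.4 × 0.4^(40f/12) and 1 − 0.2 × 0.2^(40f/12).

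| f | Control | Intervention | Exact power |
|---|---|---|---|
| 0.50 | 91.3% | 98.6% | 48% |
| 0.25 | 81.4% | 94.8% | 67% |
| 0.10 | 70.5% | 88.3% | 70% |

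**4. Drop-outs.** With the drop-out pattern of step 1, the chance of leaving before healing is γ/(λ+γ) × (1 − e^(−52(λ+γ))) = 5.2% and 3.1%, or about 3.3 and 2.0 patients of 63. On the constant-hazard curves these exceed the 1.9% and 0.1% who would still be unhealed at T2 with full follow-up.

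**5. Practice.** With a design effect of 1.1, a test with nominal critical value 1.96 has an actual level of 2 × [1 − Φ(1.96/√1.1)] = 6.2%.

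**6. Ulcer-free reading.** The article gives no recurrence rate. Assume 10% to 30% of healed patients, equally in both arms, have an open ulcer at T2. Ulcer-free proportions run from 0.981 × 0.9 = 88.3% against 0.999 × 0.9 = 89.9%, to 68.7% against 69.9%. Chi-square power is 5% to 6%. In the control arm, 0.981 × 63 × (0.1 to 0.3) = 6 to 19 patients are classified differently under the two readings.

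**The case against.** A fair defence has five parts.

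- **The text leans towards status at the visit.** Outcomes are determined at T1 and T2, and the sentence borrows the primary outcome's criteria, which can mean the state of the legs without the event date. This stands: the article does not commit to the cumulative reading. It does not settle the matter either, because photographs are sent only on a claim of healing, and no photo review at T1 or T2 is described.
- **Relapse is visible elsewhere,** through the recurrence and ulcer-count outcomes. True, and it limits the harm. But recurrence includes ulcers that closed again by T2, so subtracting it from the cumulative count does not give ulcer-free status.
- **This belongs to the analysis plan.** For the ambiguity alone that would be a good answer. The chi-square comparison, however, is a method the article does state.
- **Saturation extrapolates a planning simplification.** This stands. A reader might infer that the T2 comparison cannot separate the arms; that holds only with a constant hazard for 12 months (step 3).
- **Ulcer-free status separates the arms no better.** This also stands (step 6), unless recurrence differs between arms.

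A reader might also infer that the scoring of drop-outs would decide the T2 result. The figures do not show that. Scoring all unhealed drop-outs as failures gives 93.3% against 96.8% and power of about 14%, so neither scoring makes a significant result likely.

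**Conclusion.** The point holds in a limited form. The secondary healing count has two readings that differ for every patient with a relapse still open at the visit. The stated test ignores practice (about 6% actual level at a nominal 5%, with the plan's own design effect) and has no valid score for patients lost unhealed.

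Under the healed-by reading and the plan's exponential curves, T2 is 98.1% against 99.9% with about 3% power. With a hazard that falls after week 12, power is about 48% to 70%, so near-saturation is a consequence of the planning model and no forecast. T1 is not saturated. The size of the gap between the readings cannot be derived from the article; 6 to 19 control patients of 63 follows only from an assumed 10% to 30% relapse.

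The matter concerns a secondary outcome. The primary analysis and the sample size are unaffected.

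**What to change.** In the Secondary outcomes text and Table 4, replace the single item by two labelled quantities, and change the Statistical analysis section to match:

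1. **Proportion healed by T1 and by T2,** estimated from the time-to-healing data by Kaplan-Meier or the primary frailty model, with unhealed drop-outs censored at their last assessment, and with 95% confidence intervals. This replaces the chi-square test on counts. The 12-week rate difference already planned for the primary outcome is close to the T1 estimate.
2. **No open venous leg ulcer on either leg at T2,** taken from the ulcer count already recorded at that visit and compared with a model that includes practice. A patient who healed and has an open ulcer at T2 is then not ulcer-free.

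The second quantity makes relapse interpretable; it should not be presented as a gain in power. The cost is a change of wording and a small analysis of data already collected. The downside is that ulcer-free status rests on the unblinded practice's count, unless T2 photographs are also sent for blinded review.
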